**Seizure Outcomes**			
The proportion of participants with ≥25%, ≥ 50%, ≥ 75%, and 100% reduction (responder rates) from baseline The proportion of participants experiencing a worsening, no change, or improvement in seizure frequency from baseline	Change from baseline in the proportion of participants with a response at each evaluable visit	—	—
Seizure-free days	Change from baseline in the number of seizure-free days at weeks 4, 13, 26, and 52		
**Other Outcomes**			
CGI-S [56], CareGI-S [57]/PGI-S^b^ [58] The CGI-S and PGI-S/CareGI-S are single-item, 5-point Likert-type scales (ranging from “none” to “very severe”) that are widely used in clinical studies to assess severity of illness Using this scale, clinicians and participants/caregivers will rate their impression of the participant’s problems with behaviors and seizures	Change from baseline at weeks 4, 13, 26, and 52	Can be used for all age groups The CGI rating scales are commonly used clinician-rated measures of global symptom severity and treatment response for patients with mental disorders, but many researchers consider them to be subjective because they involve making judgments based on the clinician’s experience [59] Single-item global impression of change scales have also been used extensively in clinical trials to obtain patients’ and caregivers’ impressions of change in the condition of patients [60]	≈5 min
Treatment retention Ratio between the number of participants continuing treatment at a specific visit over the total number of participants	Retention at weeks 13, 26, and 52 after treatment initiation	–	–

^a^Completion of these participant-reported outcomes is optional in this study.

^b^The CareGI-S is required in this study, whereas the PGI-S is optional.

ABC, Aberrant Behavior Checklist; ABCL, Adult Behavior Checklist; ASD, autism spectrum disorder; ASEBA, Achenbach System of Empirically Based Assessment; ASR, Adult Self Report; BRIEF, Behavior Rating Inventory of Executive Function; BRIEF2, BRIEF Second Edition; BRIEF-A, BRIEF for Adults; BRIEF-P, BRIEF Preschool; CareGI-S, Caregiver Global Impression of Severity; CBCL, Child Behavior Checklist; CGI-S, Clinician Global Impression of Severity; CSHQ, Children’s Sleep Habits Questionnaire; NIH, National Institutes of Health; NRS: numeric rating scale; PedsQL, Pediatric Quality of Life Inventory; PedsQL FIM, PedsQL Family Impact Module; PGI-S, Patient Global Impression of Severity; PROMIS, Patient-Reported Outcomes Measurement Information System; PSQI, Pittsburgh Sleep Quality Index; QoL, quality of life; TAND, TSC-associated neuropsychiatric disorders; TAND-SQ, TSC-Associated Neuropsychiatric Disorders Self-Report, Quantified Checklist; TSC, tuberous sclerosis complex.

### TAND outcomes

TAND-specific outcomes will be evaluated using TAND-SQ, which was derived from the TAND Checklist Lifetime Version [20] and is currently being validated by the Global TANDem Consortium [19]. The caregivers will identify the single most problematic behavior and track changes over time through their responses in the TAND-SQ. The trial is designed to assess changes in TAND-associated outcomes that are of importance to the caregivers and individuals with TSC; therefore, the most problematic behavior score is being used to evaluate the caregiver’s impression of change in the problem that is most bothersome to them or the participant, regardless of the severity. Evaluation of the most bothersome symptom has been conducted previously and is recommended by the U.S. Food and Drug Administration for patient-focused drug development [61–63]. Natural TAND clusters—scholastic, neuropsychological, autism spectrum disorder-like, dysregulated behavior, overactive/impulsive, mood/anxiety, and eating/sleeping [22]—will be used to group specific neuropsychiatric characteristics for analysis. Absolute and change from baseline in TAND cluster scores, as measured by average numeric rating scale (NRS), and overall NRS TAND-related symptoms will be summarized at weeks 13, 26, and 52 by using standard descriptive statistics for continuous variables.

Given that the TAND-SQ is a relatively new instrument for assessment of outcomes specific to TSC, it will be complemented by additional well-established tools, such as Aberrant Behavior Checklist [26–32], which caregivers will use to rate the participant’s specific symptoms across the following subscales: irritability, social withdrawal, stereotypic behavior, hyperactive noncompliance, and inappropriate speech. Child Behavior Checklist (CBCL) [33,34], and Adult Behavior Checklist (ABCL) [35,36] or Adult Self Report (ASR) [36] will also be used, as applicable, on the basis of the participant’s age and ability. CBCL, ABCL, and ASR are components of the Achenbach System of Empirically Based Assessment, a validated measure to assess behavioral, emotional, and social problems and adaptive functioning across ages [37]. Changes in the overall severity of behavioral symptoms will be assessed by the caregivers/participants using the CareGI-S/Patient Global Impression of Severity (PGI-S) scale [58] and by clinicians using the Clinician Global Impression of Severity (CGI-S) scale [57,59,60].

To assess effects on specific TAND domains, additional instruments will be included, such as the Patient-Reported Outcomes Measurement Information System (PROMIS), which uses latest advances in information technology, psychometrics, and health survey research to measure patient-reported outcomes, because of the increasing focus on moving toward the use of patient-centered assessment tools [38–40]; executive functioning outcomes evaluated using Behavior Rating Inventory of Executive Function (BRIEF) [41–43,45]; and sleep outcomes evaluated using Children’s Sleep Habits Questionnaire (CSHQ) [46–48] or Pittsburgh Sleep Quality Index (PSQI) [49–51]. Additionally, Pediatric Quality of Life Inventory (PedsQL) [52,53] and the PedsQL Family Impact Module (PedsQL FIM) [54,55] will be used to evaluate QoL and family functioning.

The analysis of TAND-related outcomes will be done in participants with and those without seizure responses to CBD treatment using TAND-SQ, CBCL/ABCL/ASR, BRIEF, PROMIS, CGI-S, and PGI-S/CareGI-S to explore the TAND outcomes independent of the effect of CBD treatment on seizure outcomes.

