## Abstract

Tuberous sclerosis complex (TSC)-associated neuropsychiatric disorders (TAND) affect ≈90% of individuals with TSC and significantly reduce their quality of life (QoL). However, there are limited studies assessing pharmacotherapy for TAND. A plant-derived highly purified pharmaceutical formulation of cannabidiol (CBD; Epidiolex^®^/Epidyolex^®^ oral solution) is approved for seizures associated with TSC. Anecdotal evidence also suggests psychiatric, neuropsychological, and behavioral benefits of CBD. EpiCom (**Epi**lepsy **Com**orbidities; NCT05864846; EU-CT, 2023-507426-17), a multicenter, open-label, phase 3b/4 study, with hybrid decentralized approach, was designed in collaboration with patient advisory groups and healthcare professionals to evaluate behavioral and other outcomes following adjunctive CBD treatment in individuals with TSC-associated seizures. EpiCom will enroll participants, aged 1–65 years (United States [US]) or 2–65 years (United Kingdom [UK], Canada, and Poland), who are starting CBD for seizures and have moderate/severe behavioral challenges according to the Caregiver Global Impression of Severity scale at screening. Participants will receive CBD (up to 25 mg/kg/d based on individual response and tolerability) in addition to their standard of care (SoC) for 26 weeks, after which participants may choose to continue CBD with SoC or SoC alone for an additional 26 weeks. Key efficacy endpoints include change from baseline on the Aberrant Behavior Checklist (e.g., irritability subscale) and the most problematic behavior on the TAND-Self-Report, Quantified Checklist. Changes in executive function, sleep, QoL, family functioning, seizure outcomes (severity, responder rates, seizure-free days), retention rate, and safety will be evaluated. The trial will enroll ≈75 participants at ≈20 sites across the US, the UK, Canada, and Poland. EpiCom will assess the changes in behavioral and other outcomes associated with TAND and seizure outcomes, including overall symptom severity and treatment retention, following adjunctive CBD treatment in individuals with TSC-associated seizures. The results will inform future studies evaluating pharmacotherapy for behavioral outcomes in similar populations.

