TAND intervention evaluation studies, such as that for CBD, are complicated by the scarcity of instruments available for quantification of behavioral changes associated with TAND and are largely limited to generic instruments, which have limited validation, acceptance, or relevance for TAND [4,6]. Additionally, the TSC population is highly heterogeneous; therefore, the effect of the disorder and the treatments can be highly specific to an individual [5,6,18]. Efforts are underway to develop reliable tools that can be used to specifically evaluate TAND in the real-world setting and in clinical trials. The TAND Self-Report, Quantified Checklist (TAND-SQ), is one such tool that was developed and tested for feasibility and accessibility [19,20] and is currently being validated [21]. It is a quantifiable checklist that can be used by caregivers or individuals with TSC to assess TAND-related challenges as well as an individual’s TAND cluster profile, which includes autism-like behavior, dysregulated behavior, and eat/sleep, mood/anxiety, neuropsychological, overactive/impulsive, and scholastic clusters [6,22]. Identification of TAND clusters can help individuals with TSC and their care providers to plan for further evaluations, treatment, and support [19]. The TSC patient-reported outcome measure (TSC-PROM) for adults was recently evaluated and covers physical and mental functions, activity and participation, and social support aspects of TSC [23].

Given the rarity, complexity, and heterogeneity of TSC and TAND, and vulnerability of affected individuals as well as their caregivers, there is a greater impetus for collaborations among patients, caregivers, and HCPs in clinical trial design to drive interventions with measurable outcomes that are of value to the entire community [4,6,24]. Here we describe the study design of EpiCom (**Epi**lepsy **Com**orbidities; NCT05864846), an interventional, multicenter, open-label, single-arm, phase 3b/4 study, which was designed in collaboration with patient advisory groups (PAGs) and HCPs to evaluate behavioral and other co-occurring outcomes following treatment with adjunctive CBD in individuals with TSC-associated seizures. A primary consideration in designing the study was to evaluate endpoints that provide information on outcomes that can be evaluated in future in-depth clinical trials and are also meaningful to individuals with TSC and their families.

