**Fig 3 pone.0324648.g003:**
[figure not shown]
Study schema. *Participants who decide to discontinue CBD after the 26-week interim review visit but remain on study will form the SoC treatment arm. These participants will taper off CBD and complete a safety follow-up. ^†^Participants who decide to discontinue CBD after the 52-week final review visit will taper off CBD and complete a safety follow-up. For participants who wish to remain on CBD after the study, the 52-week final review visit is the last study visit. CBD: cannabidiol; SoC: standard of care.

During the first 26 weeks of treatment, participants will receive open-label CBD treatment in addition to the SoC. This treatment period consists of the following two phases: a 4-week titration period, during which the CBD dose will be titrated up to the participant’s optimal maximum dose (study site staff will train the participants or caregivers on how to dose and titrate CBD), and a 22-week maintenance period, during which the participants will maintain their optimal dose of CBD. Following a review after the first 26 weeks of treatment, participants will have the option to either continue adjunctive CBD treatment for another 26 weeks or discontinue CBD while maintaining their SoC treatment. Participants who choose to discontinue CBD after a 26-week interim review visit will be gradually withdrawn over a 10-day taper period and complete an end-of-taper visit and a follow-up safety assessment.

Participants who choose to continue treatment with CBD will maintain their dose for the remainder of treatment period 2, until the 52-week final review visit, which will also be the last study visit. Participants who do not continue CBD (outside of the study) after the 52-week final visit will undergo a 10-day taper period and complete an end-of-taper visit and a follow-up safety assessment. Participants will have the option to complete all study visits either at the study site or virtually (e.g., via telehealth or videoconference).

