### Statistical analysis

EpiCom is an exploratory study, so no formal statistical hypothesis will be tested. Ranking is not assigned to the study endpoints; therefore, no hierarchical testing strategy or other multiplicity adjustments will be considered. Given that the study is not controlled, no direct causal attribution of any observed association to CBD treatment will be made based on study findings. The study is not designed to distinguish whether improvements in TAND outcomes are due to CBD treatment or if they are the result of seizure reduction. A modelling approach will be used to explore the extent to which the observed associations of CBD treatment with TAND endpoints is associated with the change in seizure frequency during follow-up. Its marginal/causal effects may be further investigated with an exploratory mediation analysis [64].

Outcomes will be reported using standard descriptive statistics for continuous variables, including 95% CIs for the mean (including SD) or median (including the first and third quartiles, and the minimum and maximum values) change. Counts and percentages will be reported along with the 95% CI of the rate. Statistics will be presented overall and by age, where applicable. If provided, *P* values will be declared as nominal. An intermediate analysis at week 26 will be performed to describe any early trends.

A generalized linear mixed model (GLMM) will be used to evaluate the significant change from baseline to week 26 in effectiveness endpoints, adjusted by the assessment at baseline and age at baseline. During the second treatment period, summary statistics for endpoints may be computed for and between the CBD treatment and SoC arms. At week 52, a GLMM will be used to describe the association of treatment with change from baseline in effectiveness endpoints, adjusted by assessment at baseline, and a propensity score calculated based on age at baseline, sex, percentage change from baseline at week 26 in seizure frequency, 28-day average seizure-free days at week 26, and the number of concomitant ASMs. Least-squares means of the treatment effect (CBD vs SoC), two-tailed 95% CI and the unadjusted *P* values will be generated if at least 25% of the participants reaching the 26-week interim review will opt for SoC treatment in the second treatment period.

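### The split by seizure response is given an aim, TAND outcomes independent of the seizure effect, that the article elsewhere says the study cannot meet, and its instrument list omits the ABC

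*Protocol article*

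**What the plan says.** Four statements in the protocol article bear on this point.

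- **Aim of the split (TAND outcomes).** TAND-related outcomes will be analysed separately in participants with and without a seizure response "to explore the TAND outcomes independent of the effect of CBD treatment on seizure outcomes". The instruments are listed: "using TAND-SQ, CBCL/ABCL/ASR, BRIEF, PROMIS, CGI-S, and PGI-S/CareGI-S".
- **Limits (Statistical analysis).** The study is uncontrolled, so no observed association will be causally attributed to CBD. "The study is not designed to distinguish whether improvements in TAND outcomes are due to CBD treatment" or result from seizure reduction. A model will explore how far the TAND associations go with change in seizure frequency. Then: "Its marginal/causal effects may be further investigated with an exploratory mediation analysis".
- **Design (Introduction and Study design).** EpiCom is an "interventional, multicenter, open-label, single-arm, phase 3b/4 study". "During the first 26 weeks of treatment, participants will receive open-label CBD treatment in addition to the SoC". The only CBD versus SoC contrast comes in period 2, by the participant's own choice. Effect estimates for it are produced only if at least 25% of those reaching the 26-week review choose SoC.
- **Endpoints (Abstract and Table 1).** "Key efficacy endpoints include change from baseline on the Aberrant Behavior Checklist (e.g., irritability subscale"), together with the most problematic behavior on the TAND-SQ. Table 1 has the ABC collected at weeks 13, 26 and 52.

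**The concern.** The aim stated for the split conflicts with the limit stated under Statistical analysis. The limit is the correct one. Seizure response is a post-baseline variable in a period without an untreated group. Change among seizure non-responders is an uncontrolled before-after change in a group selected on an outcome. It contains whatever expectancy and regression to the mean the cohort has, plus any prognostic difference linked to seizure response.

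Whether behaviour improves apart from seizures is likely to be the question readers care about most, and the Abstract says the results will inform future studies. A table introduced as showing outcomes *independent* of the seizure effect invites the reader to take improvement in non-responders as a direct behavioural effect of CBD. As listed, that table would also lack the ABC. The article brings in the ABC as a well-established complement to the TAND-SQ, which is still being validated.

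**Working it through.** **1. The plan's own figure.** Sample size section: 60 evaluable at week 26 with 20% withdrawal. 60 / (1 − 0.20) = 75, which reproduces the planned enrolment. There is no power figure to check.

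**2. Can the split separate a direct CBD effect in period 1?** Write the TAND improvement of participant i as

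Y = d + t + b·S + e,

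where d is a direct CBD effect, t is everything else that moves the whole cohort (time, expectancy, regression to the mean), S is seizure improvement and b its slope. Everyone is treated, so d and t enter only as the sum d + t. A design matrix with an intercept, a treatment column and S has rank 2 of 3 because the treatment column equals the intercept. More participants do not change this.

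**3. Simulation.** n = 60, 4000 runs, all on CBD. Illustrative values, none from the article: S has mean 0.5 and SD 0.8, responder means S ≥ 0.5, residual SD of Y is 1.

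| Scenario | Responders | Non-responders | Intercept | Slope |
|---|---|---|---|---|
| d = 0.5, t = 0, b = 0.3 | 0.84 | 0.46 | 0.50 | 0.30 |
| d = 0, t = 0.5, b = 0.3 | 0.84 | 0.46 | 0.50 | 0.30 |
| d = 0.5, t = 0, b = 0 | 0.50 | 0.49 | 0.49 | 0.01 |
| d = 0, t = 0.5, b = 0 | 0.50 | 0.51 | 0.50 | 0.00 |
| d = 0, t = 0.5, b = 0, shared prognostic factor (weight 0.6 on S and Y) | 0.79 | 0.21 | 0.32 | 0.36 |

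Rows 1 and 2 cannot be told apart, nor can rows 3 and 4. In the last row seizures have no effect on behaviour, yet the groups differ and the slope is 0.6 × 0.6 / (0.8² + 0.6²) = 0.36. Neither the non-responder mean nor the intercept is a direct effect, and the slope is an association.

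**4. One artefact, for scale.** The Study population section requires a baseline score of at least 6 on the TAND-SQ item that is then followed. Expected regression to the mean is (1 − ρ)·σ·φ(z)/(1 − Φ(z)), with z = (cut − μ)/σ. The article gives none of these values. Assume μ from 5 to 7, σ = 2 and test-retest ρ from 0.6 to 0.9. With the cut at 5.5 (integer scale) the result runs from 0.1 × 2 × 0.389 = 0.08 to 0.4 × 2 × 0.964 = 0.77 points. With the cut at 6 it runs from 0.10 to 0.91. This is the shift expected in the whole cohort. Non-responders would carry it too if seizure response is unrelated to the item. It does not measure harm from the split.

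**5. Precision of the split.** The article gives no expected responder share, so assume 20% to 60% of 60, which is 12 to 36 responders. The 95% CI half-widths are then 0.64 to 0.34 SD for the responder mean, 0.29 to 0.42 SD for the non-responder mean, and 0.52 to 0.65 SD for the difference. Even as description the split is imprecise.

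**6. Mediation.** The article does not say which period or comparator it would use. In period 1 direct and indirect CBD effects are not identifiable (step 2). In period 2 exposure varies, by self-selection; the 25% condition means about 0.25 × 60 = 15 participants on SoC. Seizure change up to week 26 precedes the choice of arm, so it cannot mediate the effect of that choice.

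**7. Instrument list.** Comparing the list under TAND outcomes with the Abstract, the TAND-SQ is in both, while the ABC is in the Abstract only. No reason is given.

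**The case against.** The best defence is that the article is already candid. It says *explore*, not show. It states that no causal attribution to CBD will be made. It already plans an association model of TAND endpoints on change in seizure frequency, and since Table 1 puts the ABC under TAND outcomes, that model would cover it. The list for the split is plainly a subset, because the CSHQ, PSQI and PedsQL are absent too. The study is exploratory with no hypothesis test, and the details of an optional analysis belong in an SAP that is not shown.

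Much of this stands, and it limits the point. A reader might infer that the article claims to demonstrate seizure-independent effects of CBD. It does not: the verb is explore and the disclaimers are explicit. A reader might also infer that a mediation analysis is planned for period 1, with no variation in exposure. The text does not support that either: mediation is something that may be done, and it is tied to no period.

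What does not stand is that the disclaimers settle the matter. They contradict the aim given to the split rather than qualify it. Mean change by response group and its association with seizure change can be described; the independent reading of either cannot. An explicit list that omits a named key endpoint is also not a detail left to the SAP.

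**Conclusion.** The point holds as a contradiction in stated aims and an unexplained omission. In period 1 the split by seizure response cannot isolate a TAND effect of CBD apart from seizures. This follows from the single-arm design and needs no numerical assumption. The simulated values and the 0.08 to 0.91 point range only illustrate it and rest on assumed inputs. The marginal/causal wording has the same problem if applied to period 1, and needs a stated contrast and assumptions if applied to period 2. The weight is modest: no sample size, error rate or hypothesis test is affected. It still merits correction because it governs how a central table will be read and which instruments that table contains.

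**What to change.** - **TAND outcomes, aim.** Replace the independent-of-seizures aim with a descriptive one: *TAND change according to seizure-response status*. State that change in non-responders is not to be read as a direct CBD effect.
- **TAND outcomes, list.** Add the ABC, irritability subscale first.
- **Statistical analysis, mediation.** Drop the reference to marginal/causal effects. Alternatively, limit any mediation analysis to a contrast in which CBD exposure varies (self-selected CBD versus SoC in period 2), with a mediator measured after that choice and the assumptions stated.
- **Statistical analysis, association model.** Keep the model already planned, preferably with continuous seizure change on a scale that handles zero counts, since 100% reduction is one of the response categories. Report the slope with its 95% CI and do not read the intercept as a direct effect. An early seizure window would still overlap a baseline-to-week-26 outcome change, so it would not by itself establish time order.

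The cost is wording and one more instrument in an exploratory table; the ABC and seizure diary data are already collected. What is lost is a causal reading that the design cannot support.
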